#### Moderator and mediator analyses

For the exploratory moderator analyses, regression models will be used. In a first step, each potential moderator defined in the “Covariates” section will be tested in a separate regression model. The primary outcome FMI at t2 will be set as dependent variable. Included predictors will be group, the respective moderator variable and the interaction of group and moderator. Subsequently, a comprehensive model of all identified moderators will be estimated.

Mediation analyses will be conducted according to the principles of time-lagged mediation by Cole and Maxwell [97]. This approach will enable the establishment of temporal precedence, an important requirement for the investigation of mechanisms of change [98]. Group will be set as independent variable, whereas the variables defined in the “Potentials mediators” section as well as mindfulness (FMI) will constitute the respective mediating variables. Depression (PHQ-9), stress (PSS-4), and anxiety (GAD-7) will be chosen as outcome variables, as they have been studied most frequently in previous mediation studies in the context of mindfulness interventions [39].

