#### Covariates

To investigate potential effect-modifying influences [90], several sociodemographic as well as other variables are assessed: age, gender, nationality, marital status, study course and number of semesters, previous experience with mindfulness, psychotherapy experience, and use of additional treatment options (such as psychological counseling or psychotherapy) as well as baseline symptomatology. To examine the influence of treatment expectations on outcomes, the Client Expectancy Questionnaire (CEQ) is used, which has demonstrated high internal consistency (*α* = 0.84–0.85) [91]. It consists of six items which are measured on a 9-point Likert Scale with higher scores representing positive expectations and credibility.

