### Sample size estimation

Sample size calculations refer to detect an expected increased efficacy of StudiCare-M unguided and GoD compared to WL on the primary outcome mindfulness at t2 (post-treatment). In their meta-analysis, Spijkerman et al. (2015) found a small effect for unguided mindfulness IMIs (*g* = 0.22, 95% CI 0.10–0.34) and a significantly larger effect for guided IMIs (*g* = 0.43, 95% CI 0.30–0.56) [25]. The GoD version of our IMI provides the possibility to contact an e-coach at any time. Additionally, both the GoD and unguided versions contain various persuasive e-health technologies and that have been shown to increase efficacy and adherence (e.g., self-monitoring, goal setting, SMS prompts, automatic reminders) [63, 92]. Therefore, we assume an effect size comparable to the effects previously found for guided IMIs of *d* = 0.40. Originally, a power analysis based on a two-tailed t-test (calculated using G*Power [93]) resulted in a sample size of 133 participants per group. This was documented in the first version of the trial registration. However, in the meantime, a more precise power calculation was done by an independent biostatistician (MM). This calculation indicates that 129 participants per group are required to obtain a power of 1-beta = 90% based on *α* = .05 (taking into account clustering of participants by university and assuming an ICC = .02). Trial registration was updated accordingly. As data analysis will be based on intention-to-treat (ITT) principles, increasing sample size in order to compensate for drop-outs is not necessary.

Concerning an exploratory comparison between the UG and GoD version of StudiCare-M, the sample size is sufficient to detect a small effect of *d* = 0.20 as minimal clinically important effect difference with a power of 50% and a significance level of *α* = .05. This also corresponds to the range of effect sizes of *d* = 0.02–0.33 found for different outcome measures in the trials of Berger et al. [35] and Rheker et al. [36].

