### Statistical analyses

All data analyses will be performed after completion of data collection. Interim analysis is not considered necessary as in the context of IMIs, there are no known dangers or harms that could make a trial stop necessary. Analyses will be performed on an intention-to-treat basis. Procedures of imputation will be chosen based on patterns and mechanisms of missingness (e.g., by using multiple imputation). Additionally, per protocol analyses (based on the data of participants that completed at least 5 of the 7 core modules) will be performed to examine the impact of drop-outs on study results. Significance level for all analyses will be defined as alpha = .05. A blinded analysis of primary and secondary outcomes will be conducted by an independent researcher not otherwise involved in the execution of the study (MM).

The primary outcome FMI at t2 will be analyzed by means of linear regression models. Baseline and group will be defined as predictors. Secondary outcomes will be analyzed accordingly. Standardized mean differences with 95% confidence intervals will be calculated post-treatment and follow-up to analyze between-group effect sizes. To obtain the number of participants achieving reliable improvement in mindfulness (FMI), participants will be coded as responders and nonresponders according to the Reliable Change Index (RCI) for t2 and t3 [94]. Additionally, we will investigate potential negative effects on individual level by calculating the number of participants that display a reliable deterioration from t0 to t2 and t3 also using the RCI [95, 96]. For an exploratory examination of associations between adherence, subscription to SMS-coach, actual use of GoD, time spent practicing mindfulness exercises, and the primary outcome FMI at t2 regression analyses will be conducted.

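### Moderator models for FMI at t2 leave out baseline FMI, which the primary model for the same outcome includes; this gives up some precision on low-powered exploratory interaction tests (minor)

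*Protocol article*

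**What the plan says.** The Statistical analyses section models FMI at t2 by linear regression: "Baseline and group will be defined as predictors". I read this as baseline FMI and trial arm.

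The Moderator and mediator analyses section keeps that outcome: "The primary outcome FMI at t2 will be set as dependent variable". It then specifies one model per candidate moderator: "Included predictors will be group, the respective moderator variable and the interaction of group and moderator". A second step follows: "Subsequently, a comprehensive model of all identified moderators will be estimated".

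The candidates are listed under Covariates. They are sociodemographic variables, experience with mindfulness and psychotherapy, other treatment, and treatment expectancy, "as well as baseline symptomatology". The status of the work is explicit: "For the exploratory moderator analyses, regression models will be used". The significance level is common to everything: "Significance level for all analyses will be defined as alpha = .05".

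Table 2 shows FMI at t0, and the Randomization section places allocation after the baseline assessment. Baseline FMI should therefore be available for everyone randomized.

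**The concern.** The article gives two predictor lists for one outcome. The first contains the baseline value and the second does not, and no reason is given. An earlier measurement of the outcome is normally among its better predictors. Leaving it out puts the variance it would explain into the residual and widens the standard error of every interaction.

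The Abstract names moderators and mediators as the trial's second aim and intends the results to help choose target groups. The sample size was set for the main effect only, and no power is stated for any interaction. These tests have little precision to spare.

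**Working it through.** **Inputs from the protocol article.** 129 per group, d = 0.40, 90% power, alpha .05, ICC .02 (Sample size estimation); 1:1:1 allocation (Randomization); entry at FMI of 37 or less (Eligibility criteria). The test is taken as two-sided, since the first calculation was "a power analysis based on a two-tailed t-test".

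**Assumed.** The in-trial correlation r between baseline and t2 FMI, a moderator splitting the sample 50:50, one active arm against waitlist, and complete data.

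**The plan's own figure.** n = 2 × (1.960 + 1.282)² / 0.40² = 131.3, so 132 per group by the normal approximation; the noncentral t gives 133, the original figure. Multiplying the variance by 1 − 0.02 gives 128.7, so 129. The article does not show how 129 was reached, but this route reproduces it.

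**Interaction without baseline FMI.** There are four cells of 129 / 2 = 64.5. In SD units of the outcome, SE = √(4 / 64.5) = 0.249. Power for an interaction of size D is about Φ(D / SE − 1.96). At D = 0.40, Φ(1.606 − 1.960) = 36%. At D = 0.20 it is 12%.

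**Interaction with baseline FMI.** The residual variance is multiplied by 1 − r², so SE = √((4 / 64.5) × (1 − r²)):

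| r (in trial) | SE | SE relative to unadjusted | Equivalent sample size | Power, D = 0.40 | Power, D = 0.20 |
|---|---|---|---|---|---|
| not used | 0.249 | 1.00 | 1.00 | 36% | 12% |
| 0.3 | 0.238 | 0.95 | 1.10 | 39% | 13% |
| 0.4 | 0.228 | 0.92 | 1.19 | 42% | 14% |
| 0.5 | 0.216 | 0.87 | 1.33 | 46% | 15% |
| 0.6 | 0.199 | 0.80 | 1.56 | 52% | 17% |

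**Effect of the entry cutoff.** The article describes 37 as the medium value in the general population. If baseline FMI is normal and cut at its mean, its variance falls to 1 − 2/π = 0.363 of the population value. A population correlation ρ then becomes r = √(0.363ρ² / (1 − ρ² + 0.363ρ²)).

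- ρ = 0.5: r² = 0.0908 / 0.8408 = 0.108, so r = 0.33. The SE falls about 6% and power at 0.40 SD is about 40%.
- ρ = 0.7: r = 0.51.
- The cutoff applies to the screening score, not to the t0 score. If those two correlate 0.8, ρ = 0.5 becomes about 0.41, the SE falls about 9% and power is about 42%.

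A simulation of both regressions (2 × 129, continuous moderator, 2,000 runs per setting) agrees. With ρ = 0.5 the SE ratio was 0.87 without truncation and 0.95 with it.

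**Moderators related to baseline FMI.** If the moderator correlates 0.5 with baseline FMI, has no effect of its own, and r = 0.5, the unadjusted model already explains 0.5² × 0.5² = 0.0625 of the variance. The SE ratio is then √(0.75 / 0.9375) = 0.894, a reduction of about 11% instead of 13%.

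**The case against.** **No bias.** A reader might infer that the moderator results are biased, or that their treatment effect fails to line up with the primary analysis. Neither is supported. Under randomization, linear models with and without a baseline covariate target the same average group difference and the same interaction. The group coefficient beside an interaction term is the effect at moderator value zero, so it differs from the primary estimate whether or not baseline FMI is added. Nor does it harm the analysis that a moderator's main effect may partly carry baseline FMI, because moderation is judged on the interaction. This objection stands in full.

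**The gain is modest and its size is assumed.** A 13% smaller SE, worth a third more participants, needs an in-trial r of 0.5, which no document supports and which the entry cutoff makes less likely. An interaction of 0.40 SD is also generous, being as large as the whole assumed main effect. At half that size, power barely moves. This stands as well.

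**The comparison is a choice.** The section does not say how group is coded. With both active arms pooled against waitlist, SE = √(2/129 + 2/64.5) = 0.216, and unadjusted power at 0.40 SD is already about 46%. That changes the starting level, not the direction of the gain.

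**An article condenses, and the models are exploratory.** It can be said that the list of included predictors need not be exhaustive and that covariates belong in the analysis plan. But the article does state the predictors, directly after a primary model that names baseline. Nor does listing baseline symptomatology as a moderator fill the gap. Even if it covers FMI, FMI would enter only its own separate model, and the comprehensive model only if identified there. The exploratory label limits the severity but does not remove the point.

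**Conclusion.** The point holds as a minor one. The stated moderator models omit a covariate that the primary model for the same outcome uses and that is already collected. The cost is precision only.

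For a 50:50 moderator, one arm against waitlist (n = 258) and an interaction of 0.40 SD, power is about 36% as specified and about 39% to 52% with baseline FMI, for in-trial correlations of 0.3 to 0.6. Those correlations are assumed. The entry restriction makes the lower end more likely, and missing t2 data would lower all of these figures. The tests stay underpowered after the change, so adjustment helps without making them adequate. No confirmatory conclusion depends on it.

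**What to change.** Add FMI at t0 as a covariate to every moderator model, alongside arm, moderator and their product, and carry it into the comprehensive model whether or not it is itself identified as a moderator. Where baseline FMI is the moderator under test, enter it once.

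The cost is one phrase in the text and one degree of freedom per model, with no new data. The article places all analyses after data collection and expects collection to end in November 2020, so on its own timetable the change can be fixed before any analysis is run.

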## Discussion

Psychological problems in college students are widespread and associated with poorer academic performance. Internet-based interventions (IMIs) for enhancing mindfulness are a promising way to increase student mental health but typically suffer from low adherence, compromising the effectiveness of such interventions. This trial will be the first to examine the effectiveness of a mindfulness IMI without and with guidance-on-demand, comparing both versions to a waitlist control group as well as to each other. Additionally, we will investigate potential moderators and mediators, an area that is still understudied [25, 99].

Despite best efforts, any trial comes with certain limitations that are described in the following.

A common problem with internet-based interventions is high dropout-rates concerning both intervention and assessments. For unguided mindfulness IMIs, intervention dropout rates of 40–60% have been reported suggesting that only about half of the participants complete such interventions [29, 31]. In order to overcome this problem, we will implement the following measures: an optional SMS-Coach prompting participants every other day; the possibility to contact an e-coach any time in the “GoD” condition; and short automated feedback messages after each completed module in the “unguided” condition. Additionally, in order to receive an estimate of the true treatment effect unbiased by assessment dropout, data will be analyzed on ITT basis [100].

Within the framework of our intervention, we will not be able to track the actual amount and frequency of mindfulness practice participants will engage in. Studies have shown that the time spent practicing mindfulness in daily life is an important moderator of intervention efficacy [18]. We will however ask for the average time participants spent practicing at post-assessment and conduct a moderator analysis based on that information. Still, this retrospective assessment might be biased and a future version of StudiCare-M should include immediate tracking of mindfulness practice, e.g., in an accompanying app.

Finally, we will only include college students with moderate to low mindfulness. This approach entails a reduced generalizability of results, not allowing conclusions concerning the efficacy of our IMI for individuals already high on mindfulness. However, we decided to do so because StudiCare-M was designed as an introduction to mindfulness, primarily addressing mindfulness beginners. Consequently, this approach will allow us to evaluate the efficacy of StudiCare-M for those students who need and can therefore benefit from such an intervention the most.

Beside these limitations, our study also offers several strengths.

Many mindfulness studies so far have suffered from samples of limited generalizability. Participants were frequently recruited at only one university or from one study course [30, 34, 101, 102]. Additionally, participants sometimes received money or course credits for study participation [27–29], therefore possibly not representing real students in need. Within the StudiCare project, we are able to overcome these shortcomings. Because participants are mainly recruited via health promotion departments of more than 15 cooperating colleges in Germany, Switzerland, and Austria, we reach students from a great variety of colleges and study courses. Additionally, participants will not receive compensation for their participation reflecting “real life” conditions of health care services (except for a raffle for the long-term follow-up that they will not be informed about until the invitation to the t3 assessment). This approach enables us to learn about real-life demand for and attractiveness of our intervention, important information when it comes to long-term implementation.

So far, only few studies examined the efficacy of IMIs for college students based on acceptance and commitment therapy (ACT) [30, 31, 33, 102]. While mindfulness in general provides useful skills for stress management, ACT goes beyond meditation by emphasizing the concept of psychological flexibility and focusing on values and committed action [59]. These skills might come in specifically handy in a challenging and complex university and subsequent working life. So far, results concerning ACT-IMIs for college students have been promising but have suffered from limitations such as no long-term follow-up [31, 33] or small sample sizes [30, 31]. Our trial is designed to overcome these limitations with a large sample size as well as a 6-month follow-up.

This is one of few studies that examine the effect of “guidance on demand” (GoD) on adherence and efficacy of internet-based interventions [35, 36] and the very first to do so for a mindfulness IMI. As discussed before, mindfulness IMIs could provide an excellent possibility to reach students in need on a population level. Guided IMIs have shown to be most effective but can be associated with increased intervention costs [32]. Consequently, it is worth investigating whether a GoD-IMI for enhancing mindfulness can be effective and well accepted by participants. Additionally, we will compare GoD to an unguided version of StudiCare-M on an exploratory level. Both versions of our intervention are designed according to principles of persuasive design. Therefore, we will gather preliminary evidence on differences between persuasively designed unguided IMIs and IMIs with a minimal form of human guidance concerning effectiveness, adherence, side effects, and adverse events.

While the efficacy of mindfulness IMIs has been shown in many RCTs by now, the questions of how and for whom these interventions work have not been answered sufficiently. Therefore, this RCT will examine a range of different moderators and mediators on an exploratory level in order to contribute to this still understudied area of research [25]. Trials investigating mediators often suffer from methodological limitations such as measuring the proposed mediators, dependent and independent variables only pre- and post-treatment. Consequently, they are unable to establish chronology of change, therefore neglecting a crucial element of investigating mediators [98]. We aim to overcome this shortcoming by conducting an additional assessment at midpoint of the intervention, enabling us to find out at what time changes occur.

One last strength of this RCT is the fact that we will measure potential side effects and adverse events. It has been shown that IMIs can have negative side effects [103–105], but those have been understudied so far [104]. This is especially the case for mindfulness IMIs, where no study so far has investigated such effects. This RCT will therefore contribute to our knowledge on the safety of minimally or unguided mindfulness IMIs, an important precondition for a possible large-scale dissemination of such interventions in the future.

Going to college is associated with high stress levels and an increased risk for the development of mental disorders. Providing effective interventions to college students, helping them improve their coping and stress management skills, can therefore make a valuable contribution to the health and functionality of future society. If effective under the condition of minimal or no guidance, StudiCare-M offers a low-threshold potentially resource-efficient possibility to enhance college student mental health on a population level.

### Trial status

This is protocol version number 1.1 as submitted on 26 July 2019 and amended along reviewers’ comments on 23 October 2020. Recruitment began on 21 May 2018 and was completed by 27 April 2020. Data collection will be completed by November 2020. Prior to recruitment start, the trial was registered at the WHO International Clinical Trials Registry Platform via the German Clinical Studies Trial Register: DRKS00014774 (registration date: 18 May 2018; URL: https://www.drks.de/drks_web/navigate.do?navigationId=trial.HTML&TRIAL_ID=DRKS00014774). In case of important protocol modifications, trial registration will be updated.

## Data Availability

All principal investigators will be given full access to the data sets with the exception of MM. He will be responsible for the blinded analysis of the primary and secondary outcomes and hence will only receive a blinded version of the data needed for this analysis. The data set will be stored on password-protected servers of Ulm University with restricted access. External researchers may get access to the final trial dataset (from HB) on request depending on to be specified data security and data exchange regulation agreements. They can obtain the informed consent form in the same way. To ensure confidentiality, data dispersed to any investigator or researcher will be blinded of any identifying participant information. Anonymized results will be published in peer-reviewed journals and presented on international conferences.

## Abbreviations

ACT: Acceptance and commitment therapy
CBT: Cognitive behavioral therapy
CONSORT: Consolidated Standards of Reporting Trials
GoD: Guidance on demand
IMI: Internet- and mobile-based intervention
ITT: Intention-to-treat
RCT: Randomized controlled trial
StudiCare-M: StudiCare Mindfulness
TAU: Treatment as usual
UG: Unguided
WHO: World Health Organization
WL: Waitlist control group
